**Methods:**

This is a single-center prospective study, including 1 obese group undergoing laparoscopic Roux-en-y gastric bypass and 2 lean control groups undergoing either laparoscopic cholecystectomy or upper gastrointestinal endoscopy (n=228). During laparoscopy, biopsies will be taken of visceral fat (omentum majus), liver, muscle tissue of the abdominal wall, and subcutaneous fat. In the obese group, a small segment of the jejunum will be collected for analysis, which will be compared with an endoscopically derived jejunal biopsy from the upper gastrointestinal endoscopy control group. Stool samples for microbiota profiling will be collected at baseline and 1 year after surgery. Primary outcomes are fecal microbiota composition and mucus characteristics. Secondary outcomes include Paneth cell phenotype, body weight, diet composition, glucose tolerance, resolution of comorbidities, and weight loss 1 year after surgery.

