### Data Collection

#### Characteristics

Phenotyping of obesity will be based on measurement of body weight and calculation of BMI. Presence and severity of T2DM will be assessed by analysis of hemoglobin A1_c_ in blood, as well as analysis of plasma glucose and insulin levels, both fasting and during an oral glucose tolerance test. Presence of NAFLD will be determined on the basis of the liver biopsy, according to the validated Kleiner score [21]. Plasma levels of aspartate transaminase and alanine transaminase will be measured as markers of liver damage. Furthermore, plasma lipid spectrum, total leukocyte count, and differentiation count, as well as C-reactive protein, will be measured.

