#### Biopsies

In both the obese group and the lean control group, the following biopsies will be performed during laparoscopic surgery: visceral fat (omentum majus), liver, muscle tissue of the abdominal wall, and subcutaneous fat. In the obese group, a small segment of the jejunum will be collected during laparoscopic RYGB, a standard element of the procedure, and it will be used for analysis. In the control group, the jejunal full-thickness biopsy will be substituted by the endoscopically derived jejunal biopsy in the endoscopy group.

Directly after sampling, all tissues will be flash frozen and stored in the laboratory freezer (–80°C) until analysis. According to standard operating procedure protocol, the sampling in the obese group and lean cholecystectomy group will be performed by 3 surgeons involved in this study. The sampling in the lean endoscopy group will be performed by 1 gastroenterologist. The researcher will be present at the operating room and at the endoscopy suite at each procedure to flash freeze the samples directly after the biopsy. Stored data and materials will be only identifiable to the person by an assigned subject number. As such, patient privacy is guaranteed according to the Dutch Personal Data Protection Act.

The jejunal samples will be analyzed by means of quantitative PCR, specifically investigating HD5/DEFA5 lysozyme, mucin-1, and mucin-2, as well as Kruppel like factor 4 messenger RNA expression. Furthermore, a hematoxylin and eosin staining will be performed to allow for Paneth cell quantification. Liver samples will be taken to assess the presence and severity of NAFLD and nonalcoholic steatohepatitis, the use of the Kleiner score [21] will be done by a dedicated pathologist. Muscle tissue, visceral fat, and subcutaneous fat will be stored for future purposes to enable more detailed interorgan investigations of peripheral tissues involved in glucose and lipid homeostasis.

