### Statistical Analysis

#### Power

Sample size is calculated on the basis of the smallest expected difference in the main outcome parameter, that is, intestinal mucin-2 expression, using G*power 3 (Erdfelder, Faul, and Buchner, 1996). A pilot study with lean nondiabetic and obese diabetic rats revealed a difference in expression of 1.00±0.71 versus 0.65±0.78. Taking this into account and using a significance level of 0.05 and a power of 80%, each group will require 73 patients. Considering an expected loss to follow-up of 5%, 76 patients need to be included in each group, amounting to 228 patients in total.

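### Flash freezing of all tissue leaves, as written, no fixed portion for two secondary histological readouts: the Kleiner score in liver and the Paneth cell count in jejunum

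*Protocol article*

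**What the plan says.** The Biopsies section states the handling rule twice. The general statement is "Directly after sampling, all tissues will be flash frozen and stored in the laboratory freezer", with storage at –80°C until analysis. The second describes the researcher's task at every operation and endoscopy: "to flash freeze the samples directly after the biopsy". No fixation, division of a specimen or paraffin embedding is mentioned.

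Three uses of the tissue follow in the article:

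- **Jejunum, molecular:** "The jejunal samples will be analyzed by means of quantitative PCR", covering HD5/DEFA5, lysozyme, mucin-1, mucin-2 and Kruppel-like factor 4 mRNA.
- **Jejunum, histological:** "a hematoxylin and eosin staining will be performed to allow for Paneth cell quantification".
- **Liver, histological:** "the use of the Kleiner score [21] will be done by a dedicated pathologist". The Characteristics section makes this the definition of disease: "Presence of NAFLD will be determined on the basis of the liver biopsy, according to the validated Kleiner score".

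On rank, the Power section calls mucin-2 the main outcome: "the main outcome parameter, that is, intestinal mucin-2 expression". Paneth cell phenotype heads the secondary list in the abstract: "Secondary outcomes include Paneth cell phenotype, body weight, diet composition, glucose tolerance". NAFLD appears among the secondary objectives in the Introduction.

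**The concern.** Immediate freezing suits mRNA work. It is a less obvious choice for readouts that depend on fine morphology. As a general technical matter, ice crystals can leave vacuoles that resemble or hide fat droplets, and freezing can blur the cellular and crypt detail on which grading and counting depend. If the rule is applied as worded, both histological readouts have to be made on frozen material, and the article does not say how scoring on such material is validated.

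NAFLD is part of the study's name and, with its severity, is a focus of the cross-sectional comparison. Paneth cell properties are part of the central hypothesis. The Discussion rules out repeat biopsies at 1 year as too invasive, so a fixed baseline portion that was not kept cannot be obtained later.

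**Working it through.** **Step 1. Match each readout to the stated preparation.**

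| Readout | Tissue and groups | Method | Stated preparation | Conflict? |
|---|---|---|---|---|
| Mucin-2 and other mRNA, including HD5/DEFA5 and lysozyme | Jejunum: obese, endoscopy controls | qPCR | Flash frozen | No |
| Paneth cell quantification | Jejunum: obese, endoscopy controls | H&E | Flash frozen | Yes |
| Kleiner score, NAFLD presence and severity | Liver: obese, cholecystectomy controls | Histology, read by a pathologist | Flash frozen | Yes |

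Liver is taken only during laparoscopic surgery, so the endoscopy controls have no liver readout.

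**Step 2. Check whether the sample size is touched.** The inputs from the Power section are means of 1.00 and 0.65, SDs of 0.71 and 0.78, a significance level of 0.05 (two-tailed, from the analysis section) and 80% power.

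- Difference = 1.00 − 0.65 = 0.35.
- Pooled SD = √((0.71² + 0.78²)/2) = 0.746.
- Standardised difference = 0.35/0.746 = 0.469.
- Patients per group: 72 by the normal approximation; 72.25, rounded up to 73, by the two-sample t test. The stated 73 reproduces.
- With 5% loss: 73/0.95 = 76.8, or 77; 72/0.95 = 75.8, or 76. The stated 76 is within rounding.

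This calculation rests on mucin-2 expression measured by qPCR. No histological quantity enters it, so tissue handling changes none of these figures.

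**Step 3. Illustrate what misclassified NAFLD would do.** The documents give no sensitivity (Se) or specificity (Sp) for scoring frozen tissue. Assume that both are the same in the obese and cholecystectomy groups. For true prevalence p, the observed prevalence is Se × p + (1 − Sp) × (1 − p). Subtracting one group from the other gives:

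observed difference = (Se + Sp − 1) × true difference

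| Assumed Se = Sp | Se + Sp − 1 | Share of the true difference that remains |
|---|---|---|
| 0.95 | 0.95 + 0.95 − 1 | 90% |
| 0.90 | 0.90 + 0.90 − 1 | 80% |
| 0.80 | 0.80 + 0.80 − 1 | 60% |

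**Step 4. Treat the Paneth cell count separately.** It is a count, not a yes/no class. Random counting error in an outcome adds variance and costs precision, but it does not shift the difference between group means. The formula in step 3 therefore does not carry over, and the documents offer no figure to put in its place.

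**The case against.** The strongest reply is that this is a journal article, not the full protocol. Preparation of tissue for pathology is the kind of detail an article leaves out, and the article mentions a standard operating procedure and a dedicated pathologist. On a generous reading, freezing all tissues means that some of every tissue type is frozen, with the rest going to pathology. H&E staining can also be done on frozen sections. Part of this stands: a fixed portion may exist, and the article cannot show that it does not. It does not dispose of the point, because the article makes a positive statement about all tissues and repeats it as a task at each procedure. The reference to a standard operating procedure concerns who takes the samples, not fixation. If a fixed portion is taken, the sentence is wrong and should be corrected.

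A reader might infer several stronger things that the documents do not support:

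- **That freezing will misclassify patients.** The article says nothing about artefact and gives no error rate. Only a risk can be stated.
- **That many more patients are needed.** Any such multiple would come from assumed error rates and prevalences that nothing in the article anchors.
- **That NAFLD would be inflated in all groups.** One control group has no liver biopsy, and neither the direction nor the presence of error is known.
- **That the groups would be biased against each other.** The freezing step is the same for all. The jejunal specimens do differ, a surgical segment against an endoscopic biopsy, and might freeze differently, but that is conjecture.
- **That Paneth cell phenotype as a whole is lost.** HD5/DEFA5 and lysozyme mRNA are measured by qPCR in the same tissue and suit freezing.

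**Conclusion.** The point holds as a conflict between the stated handling rule and two planned secondary readouts. Taken as written, no fixed portion is kept for the Kleiner score, on which NAFLD status rests, or for the Paneth cell count. Grading of steatosis and steatohepatitis, and Paneth cell counting, are thereby put at risk.

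The textual conflict is clear; the size of its effect is not. The 60% to 90% range for a NAFLD prevalence difference is an illustration. It assumes sensitivity equal to specificity, between 0.80 and 0.95, with the same error in both groups that have liver biopsies. The main outcome, the other qPCR measures and the sample size are unaffected. This is a worthwhile, inexpensive improvement to secondary outcomes, not a flaw that undermines the study's main comparison.

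**What to change.** In the Biopsies section, replace the rule for liver and jejunum. Each specimen is divided at collection: one part is flash frozen for qPCR, and the other is formalin-fixed and paraffin-embedded for the Kleiner score (liver) or the H&E Paneth cell count (jejunum). Amend the description of the researcher's task to match.

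If any participants already have frozen tissue only, flag their histology as read on frozen sections and repeat the NAFLD and Paneth histology analyses without them. If a fixed portion is already taken, only the sentence about all tissues needs correcting.

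The cost is a formalin container per specimen and a short change to the sampling procedure, with no new biopsy, reader or visit. The downside is somewhat less frozen tissue per patient. The article reports recruitment as still open, so the change can protect participants yet to be sampled.

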### Statistical Analysis

#### Power

Sample size is calculated on the basis of the smallest expected difference in the main outcome parameter, that is, intestinal mucin-2 expression, using G*power 3 (Erdfelder, Faul, and Buchner, 1996). A pilot study with lean nondiabetic and obese diabetic rats revealed a difference in expression of 1.00±0.71 versus 0.65±0.78. Taking this into account and using a significance level of 0.05 and a power of 80%, each group will require 73 patients. Considering an expected loss to follow-up of 5%, 76 patients need to be included in each group, amounting to 228 patients in total.

#### Analysis of Primary and Secondary Outcome Parameters

SPSS will be used for statistical analysis (IBM Corp, Released 2013, IBM SPSS Statistics for Macintosh, Version 22.0.). A 2-tailed *P* value <.05 will be considered statistically significant. To allow comparisons among groups, data will be tested for normal distribution, and appropriate statistical tests will be applied, potentially including Students *t* test, Mann-Whitney U test, analysis of variance, Kruskal-Wallis test, Chi-square test, or Fisher exact test.

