The data on changes in gut microbiota composition after bariatric surgery are relatively limited. Within 3 months after Roux-en-Y gastric bypass (RYGB), gut microbiota has been found to be more diverse with an increased relative abundance of *Akkermansia muciniphila* [16]. However, most of the available clinical studies have small sample sizes and only analyze fecal samples collected at 12 months postoperatively or less. The possible impact of gut microbiota on failure to maintain weight loss after bariatric surgery is still unknown. This phenomenon, better known as secondary nonresponse, can occur in up to 25% of all patients who undergo RYGB surgery, and it can become apparent at 12 to 24 months postoperatively [17,18]. A recent study showed no difference in microbiota composition between a group of patients following RYGB surgery who obtained more than 50% excess weight loss after 2 years and a group of patients who did not reach that weight goal [19]. Unfortunately, that study lacked baseline samples, and that study had a very small sample size. The overall aim of the proposed study is to investigate associations among intake of dietary compounds, intestinal cell function, and gut microbiota composition. The primary objective is to determine the relationship between diet and intestinal mucin-2 expression in obesity. Secondary objectives are assessment of the relationships among diet, intestinal goblet cell and Paneth cell function, and gut microbiota composition, as well as changes in these parameters in association with secondary nonresponse, presence of T2DM, and NAFLD. We hypothesize that dietary lipid intake is associated with Paneth cell and goblet cell properties that affect gut microbiota composition.

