#### Intestinal Microbiota Composition

Participants will be provided a stool sample collection kit and will be asked to sample their stool before surgery. The samples will be stored in the home freezer (–20°C) and transported to the hospital on the day of admission, where they will be stored in the laboratory freezer (–80°C) until analysis. Participants in the obese group will be asked to provide a second stool sample at 1-year follow-up. Stool samples will be analyzed according to the shotgun metagenomics approach. By sequencing the whole genome, we will be able to compare this with a reference genome and evaluate abundance of DNA fragments. This will include detecting the 2 primary intestinal phyla—Firmicutes and Bacteroidetes—as well as *Akkermansia muciniphila* abundance. Furthermore, we will analyze the fecal samples for presence of short-chain fatty acids, that is, acetate, propionate, and butyrate.

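### Microbiota composition is primary in the abstract, secondary in the Introduction and absent from the sample size, and one P<.05 rule covers either reading

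*Protocol article*

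**What the plan says.** Four places in the protocol article bear on which outcome is primary.

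- **Abstract, Objective and Methods.** The stated primary objective covers both mucin-2 expression and microbiota composition. The outcome statement reads "Primary outcomes are fecal microbiota composition and mucus characteristics". Both items in it are families of variables, not single measures.
- **Introduction, last paragraph.** The primary objective is confined to diet and mucin-2. Microbiota is placed lower: "Secondary objectives are assessment of the relationships among diet, intestinal goblet cell and Paneth cell function, and gut microbiota composition".
- **Power.** The calculation rests on "the smallest expected difference in the main outcome parameter, that is, intestinal mucin-2 expression". No other outcome is sized, and alpha is not divided: "using a significance level of 0.05 and a power of 80%, each group will require 73 patients".
- **Statistical analysis.** Under the heading "Analysis of Primary and Secondary Outcome Parameters", a two-tailed P "value <.05 will be considered statistically significant". The section does not separate confirmatory from other tests.

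On measurement, the section on intestinal microbiota says "Stool samples will be analyzed according to the shotgun metagenomics approach". It names two phyla, *Akkermansia muciniphila* and three short-chain fatty acids, and does not say how many features will be tested. The Biopsies section lists the jejunal transcripts, among them mucin-1 and mucin-2.

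**The concern.** Microbiota composition cannot be both a primary outcome and a secondary one. The choice decides which result the study stands or falls on, and whether the 0.05 spent on mucin-2 is the whole error budget or only part of it.

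With the role left open and the same threshold applied everywhere, the status of the microbiota result could be settled after the data are seen. A microbiota P value below .05 could be presented as a positive primary outcome on the authority of the abstract. One above .05 could be treated as secondary on the authority of the Introduction. Because the abstract's two primary outcomes are families, it also does not say which variable within each family would count. The sample size gives no protection, since it was built for one test of one outcome.

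**Working it through.** **1. Reproduce the plan's sample size.** Inputs from the Power section: means 1.00 and 0.65, SDs 0.71 and 0.78, alpha 0.05, power 80%.

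- Difference = 1.00 − 0.65 = 0.35.
- Pooled SD = √[(0.71² + 0.78²)/2] = 0.746.
- Standardized difference d = 0.35/0.746 = 0.469.
- Two-sided two-sample t test at 0.05 with 80% power: n = 72.25, so 73 per group. This matches the plan. A one-sided test would need 57.

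The 73 per group therefore corresponds to a single two-sided test of mucin-2 at the full 0.05, with nothing reserved for a second primary outcome.

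**2. Family-wise error if both families are primary and unadjusted.** For k independent tests with every null true, the chance of at least one false positive is 1 − 0.95^k.

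| Tests counted | k | Chance of at least one false positive |
|---|---|---|
| Mucin-2 plus one microbiota measure | 2 | 1 − 0.95² = 9.8% |
| Firmicutes, Bacteroidetes, *Akkermansia*, mucin-1, mucin-2 | 5 | 1 − 0.95⁵ = 22.6% |

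The five are the named readouts that plausibly belong to the abstract's two primary families. Independence is an assumption. Whatever the dependence, the rate cannot exceed k × 0.05, that is 10% for two tests and 25% for five, and it cannot fall below 5%.

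**3. Cost to mucin-2 if alpha is split.** With Bonferroni at 0.025 each and the same d = 0.469:

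- Power for mucin-2 at 73 per group falls from 80.4% to 71.5% (t test), or from 80.9% to 72.4% (normal approximation); call it about 72%.
- Restoring 80% needs 87.59, so 88 per group. Allowing for 5% loss, 88/0.95 = 92.6, so 93 per group, and 3 × 93 = 279 in total against the planned 228.

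**4. Power for microbiota.** None can be computed. The article gives no effect size or SD for any microbiota measure.

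**5. How many tests would make a false positive nearly certain.** 1 − 0.95⁵⁸ = 94.9% and 1 − 0.95⁵⁹ = 95.2%, so about 59 independent tests are needed to reach 95%.

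**The case against.** The best defense concerns the analysis section. It states a conventional threshold, does not say that P values will be unadjusted, does not mention taxa, and lists its tests only as possibilities. Handling of multiplicity for sequencing data is commonly left to a full protocol or analysis plan, and neither is shown. The Discussion describes the study as exploring associations and concedes that it cannot prove causality. Sizing a study on one main outcome is also normal practice. All of this stands: the absence of a false discovery procedure is not in itself a fault of the article, and the lack of microbiota power is a defect only if microbiota is truly co-primary.

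A reader might go further and infer that false positives are near certain because the stool is sequenced by shotgun metagenomics. The documents do not support that. They do not give the number of features tested or describe species-by-species testing. A figure such as 200 species, with 0.05 × 200 = 10 false positives, is an assumption about both the count and the plan, and correlation between taxa lowers the chance of at least one.

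A reader might also count every named laboratory readout, 11 in all (three taxa, three fatty acids, five transcripts), and quote 1 − 0.95¹¹ = 43% as the error rate for a primary claim. That mixes categories. The abstract makes Paneth cell phenotype secondary, the fatty acids are described as a further analysis, and mucin-2 is the outcome for which the study expects a difference. Even the five-readout figure is approximate, because the Introduction describes Firmicutes and Bacteroidetes as moving in opposite directions on high-fat diets.

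None of this removes the conflict between the abstract and the Introduction. A condensed article may omit detail, but both definitions are printed in it and they disagree.

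**Conclusion.** The point holds as a contradiction about the primary outcome, made consequential by a threshold that treats primary and secondary outcomes alike. The abstract makes microbiota composition primary; the Introduction and the Power section make mucin-2 the sole primary target and spend all of alpha on it.

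Under the abstract's reading with no adjustment, the family-wise error is 9.8% for one test per family and about 23% for the five named readouts. Both figures assume independent tests and true nulls. Anything higher rests on an unstated number of taxa. If alpha is split in two instead, mucin-2 power at the planned 73 per group is about 72%, not 80%, given the plan's own effect size.

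Confidence is high on the contradiction. It is lower on the multiplicity part, because a plan not shown may qualify the rule.

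**What to change.** Reconcile the abstract's Objective and Methods, the Introduction and the Power section:

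- **Name one primary outcome.** Make jejunal mucin-2 expression the single primary outcome, tested at two-sided 0.05. The Introduction and Power section already read this way, so the sample size does not change. List microbiota composition as secondary in the abstract.
- **Record the change.** Recruitment has been open since early 2016 and the abstract now calls microbiota primary, so this is a change of printed outcome status. Date it as a clarification and make it before outcome data are examined.
- **Limit the significance rule.** In the analysis section, reserve confirmatory significance for the primary outcome. Put metagenomic and other secondary readouts under false discovery control, or label them exploratory.

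If the investigators intend microbiota to be co-primary, they should name one microbiota measure, split alpha (for example 0.025 each), restate mucin-2 power at 73 per group as about 72%, and supply an effect size for the microbiota measure. Restoring 80% for mucin-2 would take 88 per group before losses.

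The first route costs some rewording, a dated record and fewer nominal secondary claims. The second costs power or patients.
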